# Traditional Chinese medicine for stable angina pectoris via TCM pattern differentiation and TCM mechanism: study protocol of a randomized controlled trial

**DOI:** 10.1186/1745-6215-15-422

**Published:** 2014-10-30

## Abstract

**Background:**

Stable angina pectoris is experienced as trans-sternal or retro-sternal pressure or pain that may radiate to the left arm, neck or back. Although available evidence relating to its effectiveness and mechanism are weak, traditional Chinese medicine is used as an alternative therapy for stable angina pectoris. We report a protocol of a randomized controlled trial using traditional Chinese medicine to investigate the effectiveness, mechanism and safety for patients with stable angina pectoris.

**Methods/Design:**

This is a north-east Chinese, multi-center, multi-blinded, placebo-controlled and superiority randomized trail. A total of 240 patients with stable angina pectoris will be randomly assigned to three groups: two treatment groups and a control group. The treatment groups will receive Chinese herbal medicine consisting of *Yi-Qi-Jian-Pi* and *Qu-Tan-Hua-Zhuo* granule and *Yi-Qi-Jian-Pi* and *Qu-Tan-Hua-Yu* granule, respectively, and conventional medicine. The control group will receive placebo medicine in addition to conventional medicine. All 3 groups will undergo a 12-week treatment and 2-week follow-up. Four visits in sum will be scheduled for each subject: 1 visit each in week 0, week 4, week 12 and week 14. The primary outcomes include: the frequency of angina pectoris attack; the dosage of nitroglycerin; body limited dimension of Seattle Angina Questionnaire. The secondary outcomes include: except for the body limited dimension of SAQ, traditional Chinese medicine pattern questionnaire and so on. Therapeutic mechanism outcomes, safety outcomes and endpoint outcomes will be also assessed.

**Discussion:**

The primary aim of this trial is to develop a standard protocol to utilize high-quality EBM evidence for assessing the effectiveness and safety of SAP via TCM pattern differentiation as well as exploring the efficacy mechanism and regulation with the molecular biology and systems biology.

**Trial registration:**

Clinical Trials Registration: ChiCTR-TRC-13003608, registered 18 June 2013.

**Electronic supplementary material:**

The online version of this article (doi:10.1186/1745-6215-15-422) contains supplementary material, which is available to authorized users.

## Background

Stable angina pectoris (SAP) due to coronary heart disease (CHD) is defined as a major clinical manifestation of trans-sternal or retro-sternal pressure or a choking sensation or pain, which is caused by coronary insufficiency, myocardial ischemia, and hypoxia on the basis of an atherosclerotic coronary vascular lumen [1, 2]. According to World Health Organization (WHO), CHD is one of the major causes of death and has drawn the attention of traditional Chinese medicine (TCM) and western medicine (WM) researchers. In China, the prevalence and incidence of SAP are 2.4% in males and 3.2% in females, which is a serious social problem in view of its large population basis [3]. Its treatment is mainly relief of symptoms with anti-anginal medications or revascularization procedures. The anti-anginal medications are selected from three groups of anti-anginal chemical drugs including β blockers (BBs), calcium channel blockers (CCBs) and nitrates [4]. In China, a large majority of SAP patients resort to Chinese herbal medicine, acupuncture and other TCM therapies [5].

As for SAP, phlegm has become the popular trend of TCM pattern elements. The relationship between spleen deficiency generating phlegm and SAP has been recorded in the *Inner Canon of the Yellow Emperor* (*Huangdi Neijing*). Correspondingly, phlegm and spleen deficient is one of the main TCM patterns of SAP in terms of recent studies [6, 7].

The TCM pattern is a characteristic profile of clinical signs and symptoms manifested by a group of patients [4]. Wang Yong-yan, Academician of Chinese Academy of Engineering, postulated that TCM pattern had the performance characteristics that included reality inside and virtual outside, spatiotemporal dynamic, multi-dimensional interface [8] . Lu Guang-xin, TCM master, announced that the TCM pattern was the core concept and logical starting point of pattern differentiation, which contained the property of diagnostics, pathophysiology, and therapeutics [9, 10]. Hence, we may believe that TCM pattern is a physiological regulation network, which contains a regulation center, overall effective target, material basis and functional unit. Its mechanism needs to be indicated by means of TCM pattern prevention and treatment characteristics, multiple organ integration effectiveness, and functional unit network so as to guide clinical practice as well as for inspiring basic research.

Systems biology, defined as multiple comics integration and consolidation from genes, cells, the organization of individuals, is the TCM pattern efficacy and mechanism research method fitting with TCM theory, characteristics and discipline [11–13]. Hence, we utilize high throughput screening (HTS) technology of systems biology; that is transcriptomics, metabonomics, proteomics, and so on, to promote fundamental research of TCM pattern, global Chinese compound medicine selection, evaluation and technology platform. In recent years, a comprehensive approach has shown the TCM efficacy mechanism of SAP in the view of regulating lipid metabolism abnormality and resisting inflammatory expression and endothelial dysfunction [14]. However, there is not adequate understanding of the interaction and relationship between spleen deficiency generating phlegm of SAP (response system) and regulation from spleen (intervention system) through the scattered and small-scale reduction biological research. Notably, we should explore the clinical evaluation and efficacy mechanism and regulation on the foundation of systems biology and evidence-based medicine (EBM).

In this trial, we intend to investigate the efficacy mechanism for SAP with spleen deficiency and phlegm pattern through brain-gut axis regulation of lipid metabolism, immune inflammation and vascular endothelial network. Meanwhile, we attempt to further validate the effectiveness and safety in light of clinical efficacy evaluation index, which is the frequency and duration of angina pectoris attacks, health-related quality of life, and so on.

## Methods/Design

### Study design

This is a north-east Chinese, multi-center, multi-blinded, placebo-controlled and superiority randomized trail with three parallel groups. The study protocol was based on strict and scientific recommendations in the Consolidated Standards of Reporting Trials (CONSORT) statement [15] and SPIRIT 2013 Statement [16]. This trial was supported financially by the National Basic Research Program of China ‘973 Program’ (Number 2013CB531704). The trial was registered in Chinese ClinicalTrials.gov with approval number ChiCTR-TRC-13003608.

Two hundred and forty participants will be recruited at six large comprehensive hospitals in China, which are: Affiliated Hospital of Liaoning University of TCM, Liaoning Institute of Chinese Medicine, Affiliated Hospital of Inner Mongolia National University, Shen-Zhou Hospital of Shenyang Medical College, First Affiliated Hospital of China Medical University, and Sheng-Jing Hospital of China Medical University. After a two-week run-in period, eligible subjects will be randomly assigned to one of 3 groups, *Yi-Qi-Jian-Pi* and *Qu-Tan-Hua-Zhuo* group (Group 1), *Yi-Qi-Jian-Pi* and Qu-Tan-Hua-Yu group (Group 2), and the placebo group. All three groups then underwent a 12-week treatment and a 2-week follow-up period. The flow chart is listed in Figure 1.

**Figure 1 Fig1:**
[figure not shown]
**Trial flow chart.**

### Randomization and allocation concealment

A total of 240 patients will be randomly assigned in a ratio of 1:1:1 using the statistical package. To guarantee rigorous methodology, stratified block randomization and central coordination will be initiated. The unique code will be assigned to each newly eligible participant and properly preserved in the trial management board. This procedure ensures each eligible patient having an equal probability of being assigned to three different groups, which will not be influenced by the researchers. A statistician expert of the Beijing Bozhiyin Science and Technology Co. Ltd, Beijing, China will act as the coder and they will be shielded from patient recruitment.

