### Sample size calculation

According to the response rates of treatment, Group 1 and placebo were 88.5% and 60%, respectively; 37 patients of each group was estimated as sufficient to achieve 80% power in detecting treatment differences, based on two-sided Chi-square test without continuity correction at a significance level of 0.05 (α = 0.05; 1-β = 0.80). In the same way, assuming the clinical effective rates of Group 2 and placebo were 82.5% and 60%, respectively and 64 patients of each group was estimated as sufficient to achieve 80% power. Meanwhile, taking into account a dropout of 15%, we concluded that a total of 240 patients with 80 for each group would need to be recruited to ensure statistically significant results.

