### Statistical analysis

The statistical analysis will be conducted by a statistician of the Beijing Bozhiyin Science and Technology Co. Ltd, China. They are blinded to the whole trial and using Statistical Analysis System (SAS, Cary, NC, USA) version 9.2 and Statistic Package for Social Science (SPSS, Chicago, IL, USA) version 17.0 software packages. All mechanism, efficacy and safety analyses will be strictly conducted according to the intention-to-treat (ITT) principle and the full analysis set (FAS) population, the per-protocol set (PPS) population and the safety set (SS) population. Missing values will be replaced by the last observation carried forward (LOCF) method.

The statistical significance is defined as a two-sided *P*-value of <0.05 and 95% confidence interval. For descriptive statistics, continuous variables will be described as numerous, mean ± standard deviation, median, Q1 to Q3 and mini-maxi and dichotomous data will be reported as frequency and percentage. Baseline differences among the groups will be assessed with the use of Student’s *t*-test for normally distributed continuous variables and the non-parametric Mann-Whitney *U*-test for non-normally distributed variables. Comparisons between groups will be conducted by using an analysis of covariance (ANCOVA) with baseline as covariate. For efficacy analysis, changes from baseline to endpoint of treatment in scores will be tested with repeated measure analysis of variance (ANOVA). Within group differences will be assessed with paired *t*-test for normally distributed data and Wilcoxon signed-rank test for non-normally distributed data. Mechanism will be assessed between mechanism index and primary outcomes by ANCOVA and regression analysis. Safety will be assessed by participant compliance and adverse events. The endpoint events will be listed by detailed account.

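### Randomisation is stratified, but the stated ANCOVA and repeated-measures models name no stratification factor; if the strata are prognostic, the analysis is conservative and forgoes some power

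*Protocol article*

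**What the plan says.** Under Randomization and allocation concealment, the article states "A total of 240 patients will be randomly assigned in a ratio of 1:1:1" and that "stratified block randomization and central coordination will be initiated". No stratification factor is named there or elsewhere in the article.

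Under Study design, "Two hundred and forty participants will be recruited at six large comprehensive hospitals in China". The article does not say that hospital is a stratification factor. In a six-hospital trial it is the likely candidate, but that is an inference.

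Under Statistical analysis, the between-group model is given as follows: "Comparisons between groups will be conducted by using an analysis of covariance (ANCOVA) with baseline as covariate". The next sentence assigns the change in scores over the treatment period to a repeated-measures ANOVA. Neither sentence mentions a stratum or centre term.

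Under Sample size calculation, the trial is sized on response rates, "based on two-sided Chi-square test without continuity correction at a significance level of 0.05" with "α = 0.05; 1-β = 0.80", so no covariate adjustment enters the planned number.

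**The concern.** Stratified blocks keep the arms balanced within each stratum. Differences between strata then largely cancel out of the treatment comparison, and the true variance of the estimated effect falls. A model that leaves the strata out does not know this and still counts between-stratum variation as error. Its standard error describes a less precise trial than the one that was run. Confidence intervals come out too wide and P-values too large.

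This happens only if the strata predict outcome beyond what the baseline value already explains. If they do, the true type I error is below the nominal 5%, and part of the precision gained by stratifying does not reach the reported result.

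**Working it through.** **Inputs from the article.** Allocation is 1:1:1 in 240 patients at six hospitals, with a two-sided α of 0.05 and 80% power. Baseline is the only covariate named.

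**Assumed input.** R² is the share of post-baseline residual variance explained by the strata. The article gives no figure, so the range 0 to 0.20 is used.

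**The plan's own figure first.** For "Group 1 and placebo were 88.5% and 60%, respectively; 37 patients of each group" the formula is the two-proportion sample size with pooled variance under the null and no continuity correction:

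n = [1.96·√(2p̄(1−p̄)) + 0.8416·√(p₁(1−p₁) + p₂(1−p₂))]² / (p₁−p₂)²

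- Group 1 against placebo (0.885, 0.60; p̄ = 0.7425): (1.212 + 0.492)² / 0.285² = 35.8, so 36. Stated: 37.
- Group 2 against placebo (0.825, 0.60; p̄ = 0.7125): (1.255 + 0.522)² / 0.225² = 62.3, so 63. Stated: 64.
- Dropout of 15%: 64 / 0.85 = 75.3, so 76 per group and 228 in all. The planned 80 per group and 240 in all exceed this.

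The stated sizes reproduce to within one patient. They rest on an unadjusted test, so the choice of covariates does not alter them.

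**Effect of omitting the strata.** Set the residual variance to 1 and assume the arms are balanced within strata. The true standard error is then proportional to √(1−R²), while the model without strata reports one proportional to 1.

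- Inflation of the reported standard error: 1/√(1−R²)
- True type I error without strata: 2·[1 − Φ(1.96/√(1−R²))]
- Power without strata: Φ((2.80 − 1.96)/√(1−R²))
- Power with strata: Φ(2.80/√(1−R²) − 1.96)

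Here 2.80 = 1.96 + 0.84 is the standardised effect that gives 80% power without adjustment at R² = 0.

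| R² (assumed) | SE too large by factor | Type I error without strata | Power without strata | Power with strata | Points forgone |
|---|---|---|---|---|---|
| 0 | 1.000 | 5.0% | 80.0% | 80.0% | 0 |
| 0.01 | 1.005 | 4.9% | 80.1% | 80.4% | 0.3 |
| 0.05 | 1.026 | 4.4% | 80.6% | 82.0% | 1.4 |
| 0.10 | 1.054 | 3.9% | 81.3% | 84.0% | 2.7 |
| 0.20 | 1.118 | 2.8% | 82.7% | 88.0% | 5.3 |

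**Check by simulation.** The setting was six centres of 40 patients, blocks of three, a baseline–outcome correlation of 0.5 and 6,000 runs per setting, with ANCOVA fitted with and without centre. With centre carrying an assumed 10% of the outcome variance:

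- The mean reported standard error was 0.138 without centre and 0.130 with it. The empirical standard error was about 0.13 under either model.
- Type I error was 3.6% without centre and 4.8% with it.
- Power was 80.4% without centre and 83.8% with it.

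The simulated 10% is a share of total variance rather than of post-baseline residual variance, so it need not match the R² = 0.10 row exactly. The direction and size agree. With no centre effect the two models were indistinguishable (power 80.7% and 80.8%).

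**The case against.** The strongest objection is that a condensed article may leave the stratification factors and the full covariate list to documents not shown here, and that naming baseline does not expressly exclude anything else. This stands as far as the unnamed factor goes: not naming it in the article is no error. It does not remove the mismatch, because the article states both the randomisation method and the model, and the model as stated lacks the strata. An analysis plan that added them would depart from the published sentence.

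A second objection is that stable differences between strata in attack reporting or nitroglycerin use would also show in the baseline value, which the ANCOVA already includes. The remaining R² could then be close to zero, and so could the loss. This stands, and it is why the range starts at 0.

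A reader might go further than the article allows in four ways.

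- *That randomisation is stratified by hospital.* The article does not say so.
- *That power falls below the planned 80%.* If the adjusted analysis is set at 80%, the unadjusted one works out at 79%, 77% and 73% for R² of 0.05, 0.10 and 0.20. But the trial was sized on an unadjusted test. Anchored to 80% unadjusted power at R² = 0, the stated analysis stays at or above 80% throughout the table.
- *That the benefit of stratifying is cancelled.* Power without strata rises with R² in the table, because the balance still reduces the true variance. Only part of the gain is left unused.
- *That the stated analysis is invalid or biased.* The error is on the conservative side.

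**Conclusion.** The point holds as a conditional loss of efficiency. That the stated models do not include the strata, and that the effect is conservative, can be said with confidence. The size cannot be fixed from the article, because it depends on an R² that is not given: nothing at 0, negligible at 0.01, modest at 0.05 to 0.10, and about five points of power at 0.20. These figures assume balance within strata and an effect giving 80% unadjusted power at R² = 0. The false-positive rate is not inflated and the sample size needs no change. The change is worth making because it costs almost nothing, but the trial's validity does not depend on it.

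**What to change.** Name the stratification factor or factors, and change the model sentence to: *ANCOVA with baseline value and the randomisation stratification factor(s) as covariates*. Include the same factor or factors in the repeated-measures model. Settle this before unblinding, so that the choice of adjustment cannot depend on the results; the article reports recruitment as still under way at submission.

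The cost is one clause. If hospital is a stratification factor, six hospitals use 6 − 1 = 5 degrees of freedom among 240 patients. If the strata turn out not to be prognostic, almost nothing is lost; if they are, the test returns to its nominal level and the forgone power is recovered.

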### Blinding

This trial is a multi-blinded design and researchers, participants, drug management staff, data collection staff and statisticians will be blinded during the trial period. When an emergency occurs (such as a serious adverse events), or doctors must know the treatment of patients who require intervention, the researcher should immediately inform the main researcher to unblind the central random system. Moreover, the main researchers and trial monitors will be informed immediately. Once the blind letter is open following an emergency, the participant will be eliminated from the trial and the researcher should note the reason, blind time and place of uncovering in the Case Report Forms (CRFs) together with the main researcher, Institutional Review Board (IRB) and staff who perform the unblinding.

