### Handling of withdrawal and dropout

Voluntarily withdrawalLoss of follow-upPoor compliance and presence of severe adverse effectsRevealing and uncovering blind in urgencyMisdiagnosisUsing forbidden drugs or treatments in the course of the trialTaking no medication during the trialNo evaluable records after medication

Reasons for withdrawing participants will be recorded in CRFs, and the last data would be included in data analysis.

The whole research plan would be terminated for the following circumstances:Occurrence of serious adverse events related to the research medicationFlawed protocolFunding and management problem due to the sponsorsAdministrative authorities terminate the trial

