#### Endpoint outcomes

Death incident: cardiovascular death, cerebrovascular death, sudden death, other cause of death.

Cardiovascular incident: unstable angina pectoris hospitalization, acute myocardial infarction, malignant arrhythmia, cardiac shock, revascularization and other cardiovascular incident.

Non-cardiovascular incident: stroke, pulmonary embolism, peripheral vessel, tumor, other non-cardiovascular incident.

All three groups will undergo a twelve-week treatment and two-week follow-up. Four visits in sum will be scheduled for each subject: one visit each in week 0, week 4, week 12 and week 14. The CRFs contains a range of information and this will be completed by the corresponding researchers at each center. Trial coordinators and therapists at each center will record above endpoint outcome and the details of these events throughout the treatment and follow-up period. Outcomes to be measured and the time points of data collection can be found in Additional file 1: Table S1.

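### Ending participation after a code break or other post-randomization event stops outcome and event collection, so LOCF can put a value from before a deterioration in place of the week-12 outcome

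*Protocol article*

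**What the plan says.** Blinding gives the trigger for breaking the code: "When an emergency occurs (such as a serious adverse events), or doctors must know the treatment of patients who require intervention". The consequence follows: "Once the blind letter is open following an emergency, the participant will be eliminated from the trial".

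Handling of withdrawal and dropout lists emergency unblinding again. Beside it stand poor compliance, severe adverse effects, misdiagnosis, use of forbidden drugs and other reasons. One rule covers the data of all of them: "Reasons for withdrawing participants will be recorded in CRFs, and the last data would be included in data analysis".

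Statistical analysis states the principle: "All mechanism, efficacy and safety analyses will be strictly conducted according to the intention-to-treat (ITT) principle and the full analysis set (FAS) population". It also names a PPS and a safety set, and adds: "Missing values will be replaced by the last observation carried forward (LOCF) method".

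Endpoint outcomes sets the schedule, "one visit each in week 0, week 4, week 12 and week 14", and says that site staff "will record above endpoint outcome and the details of these events throughout the treatment and follow-up period". It does not say whether this continues for a participant who has been eliminated.

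**The concern.** Every one of these reasons arises, or is acted on, after randomization. An ITT analysis needs outcomes on all randomized patients, including those who stop the study medicine. The article offers no state in which a patient is off the granules but still followed, so applying the rules as written ends outcome collection too.

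Some of the reasons are tied to how the patient is doing. A code break is prompted by a serious adverse event or a need for intervention. The forbidden list (Concomitant treatments and forbidden drugs) bars nitrates other than nitroglycerin and non-dihydropyridine CCBs. The Background names nitrates and CCBs as anti-anginal drugs, so a patient whose angina worsens could plausibly meet that withdrawal reason.

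Two things are at stake. The primary outcomes (attack frequency, nitroglycerin dosage, one SAQ dimension) may be represented by a value from before the deterioration. And an event after a code break, such as a death following an infarction, may not be captured.

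**Working it through.** **1. What happens to a withdrawn patient's data**

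Taking the scheduled visits as the only assessments (the detailed timetable is in an additional file that is not shown):
- Leaves before week 4: the last value is baseline, week 0, and LOCF carries it to week 12.
- Leaves between weeks 4 and 12: the last value is week 4. A patient eliminated in week 8 because of an event that week is analysed at week 12 on a measurement taken four weeks before the event.
- Leaves after week 12: the end-of-treatment value is observed; week 14 and any later events are not.

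The patient stays in the denominator, but the outcome is not the one that occurred. A carried week-4 value can be too favourable. A carried baseline value can deny a patient credit for improvement. The direction is therefore not fixed.

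**2. The plan's own sample size**

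Inputs from Sample size calculation: 88.5% against 60%, 82.5% against 60%, two-sided chi-square test without continuity correction, α = 0.05, power 0.80, dropout 15%, 80 per group. The pooled-variance formula is

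n = [1.96·√(2p̄(1−p̄)) + 0.842·√(p₁(1−p₁)+p₂(1−p₂))]² / (p₁−p₂)².

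- Group 1: 36 per group (stated 37).
- Group 2: 63 per group (stated 64).
- With dropout: 64/0.85 = 75.3, so 76. The planned 80 leaves 80 × 0.85 = 68, with Group 2 power 0.83.

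The stated figures reproduce. The allowance covers lost numbers; it cannot correct a biased value.

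**3. Illustration of size**

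Assumed, not in the documents: in one arm only, 5% of patients (0.05 × 80 = 4) are true non-responders whose carried-forward value counts as a response. For scale, 15% dropout is 0.15 × 80 = 12 per arm; the article does not say how many would come from these rules. With n = 80 per arm, the rejection probability is

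Φ[(d − 1.96·s₀)/s₁] + Φ[(−d − 1.96·s₀)/s₁], where s₀ = √(2p̄(1−p̄)/n) and s₁ = √([p₁(1−p₁)+p₂(1−p₂)]/n).

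| Case | Rates | d | s₀ | s₁ | Rejection |
|---|---|---|---|---|---|
| Group 2 as planned | 82.5% v 60% | 0.225 | 0.0716 | 0.0693 | 0.89 |
| No true effect, 5% in the active arm | 65% v 60% | 0.050 | 0.0765 | 0.0764 | 0.095 + 0.004 = 0.10 |
| Group 2 effect, 5% in control | 82.5% v 65% | 0.175 | 0.0696 | 0.0682 | 0.71 |

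At an assumed 10%, the last two rows become 0.26 and 0.46. If the same 5% arose in both arms with no true effect (65% v 65%), rejection stays at 0.05: it is imbalance that inflates the error. The response rate is used because it is the only outcome for which the article gives figures; bias in the named primary outcomes cannot be computed from it.

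**The case against.** A reader might infer from the word eliminated that these patients are deleted from the analysis and that the plan therefore contradicts its ITT statement outright. The documents do not support this. The withdrawal section lists emergency unblinding among the reasons whose last data are kept, LOCF fills the gaps, and the PPS is a separate set. Calculations that delete non-responders from the denominator would model a rule the plan does not state. For example, 10% lost from one arm turns 60% into 0.60/0.90 = 66.7%.

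A reader might also infer that all the listed reasons selectively remove patients who are doing badly. That is likely for code breaks and severe adverse effects, and plausible for forbidden drugs. Nothing shows it for misdiagnosis or poor compliance, and no rates by arm are given.

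On events, the endpoint section does not exempt eliminated patients, the reason for a code break goes into the CRF, and endpoint events are to be listed without a stated between-arm test. A missed later event would thus leave the listing incomplete and would not change the primary comparison.

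Finally, set definitions are often left to an analysis plan. That is fair for the detail of the FAS and PPS. It does not answer the main point: the elimination rule is written in the protocol itself, and an analysis plan cannot recover outcomes that were never collected.

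**Conclusion.** The concern holds in a limited form. The protocol ends participation for post-randomization reasons, some probably related to outcome, and does not provide for continued collection. This undercuts the ITT analysis and the recording of events throughout follow-up, without formally contradicting either. The size and direction of bias are unknown. The figures of about 10% rejection under no effect, and Group 2 power falling from 0.89 to 0.71, rest on an assumed 5% misclassification confined to one arm. They show what a few patients per arm could do; they are not an estimate of the plan's error rate. The sample size is unaffected. Recruitment was under way when the article was submitted (Trial status), so early correction matters.

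**What to change.** - In Blinding, replace elimination from the trial with: the code break is recorded, and outcome and event collection continues at the scheduled visits to week 14 unless the participant withdraws consent for follow-up.
- Apply the same rule to severe adverse effects, forbidden drugs, poor compliance and misdiagnosis, and state that these reasons exclude a patient from the PPS only.
- Analyse all randomized patients in their allocated arm, using the values actually observed after treatment stops or the code is broken.
- For what still remains missing, do not rely on LOCF alone: replace it as the sole method, or test it by sensitivity analysis.

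No change to any patient's treatment is proposed. The cost is a short amendment, a CRF instruction and the small effort of following off-treatment patients at visits that already exist.
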